MBCT offers a number of advantages for addressing more persistent courses of depression. Mindfulness training is specifically aimed at helping patients become better at recognising and disengaging from habitual and automatic maladaptive patterns of thinking. Research indicates that, through such ‘decentering’, the practice helps to prevent the spiralling of negative mood [16]. The training provides patients with sustainable skills that remain accessible to them after the end of the intervention, with recent evidence suggesting that ‘decentering’ skills further improve as patients continue using mindfulness practices following the end of the intervention [17]. MBCT might thus serve to effectively reduce symptoms [11, 12] as well as keep people well for the longer term [18]. Because of its group-based format and emphasis on training skills, the intervention is particularly suited for alternative forms of delivery such as videoconferencing.

In order to provide evidence that, if positive, would be sufficient to enable a change in IAPT practice, we shall compare MBCT (in addition to TAU) as delivered via videoconferencing to treatment-as-usual (TAU) in IAPT high-intensity treatment non-responders in a definitive clinical trial. TAU was chosen as the comparator as it is reflective of the current state of care. Delivery via videoconferencing was chosen due to demands of the COVID-19 pandemic. We shall test the immediate effects of the intervention on depressive symptomatology as well as whether effects on symptomatology can be sustained over a period of 6 months (the primary outcome), thus taking into account the high risk of relapse in early stages following treatment. In addition to testing clinical effectiveness, we shall measure service use and collect information on quality of life in order to provide information on the cost-effectiveness of the intervention in IAPT high-intensity treatment non-responders. Previous research has suggested that MBCT for relapse prevention is broadly comparable to maintenance antidepressant use with an estimated cost for group attendance in person of £112 per group participant [19] with these costs likely to be lower when delivering the intervention via remote formats such as videoconferencing. However, data on the economic effects of outcome in IAPT non-responders would be needed in order to guide decisions on implementation in this particular group.

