### Hypotheses

We hypothesise:That participants who receive MBCT will show significantly stronger reductions in depressive symptomatology than participants who receive TAU both at 10 weeks post-randomisation (post-treatment; secondary outcome) and at 34 weeks post-randomisation (primary outcome).That the MBCT intervention will be cost-effective either in terms of reductions in costs elsewhere in the health system or in improvements in outcomes at 34 weeks post-randomisation.

We will also investigate effects on a range of other secondary outcomes including measures of co-morbid anxiety symptoms, social functioning and quality of life as well as potential process variables including decentring and mindfulness (see further below).

Qualitative analyses will investigate acceptability and implementability of MBCT taking into account the particular type of delivery format chosen.

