#### Secondary outcomes

Secondary outcomes include PHQ-9 measured at 10 weeks post-randomisation, and other clinical outcomes measured at 10-week and 34-week follow-up. The authors report a test–retest reliability of 0.84 over a period of 48 h [20]. Other clinical secondary outcome measures will include the Generalized Anxiety Disorder Questionnaire (GAD-7) [24], the Phobia Scale and the Work and Social Adjustment Scale, all from the IAPT minimum data set (IAPT Toolkit, 2008/9), along with the Warwick-Edinburgh Mental Wellbeing Scale (WEMWBS) [25], Experiences Questionnaire (EQ) Decentering Scale [26] and Five Factor Mindfulness Questionnaire (FFMQ) [27]. A series of binarised outcomes will be derived, based on PHQ-9 and/or GAD-7. Recovery, reliable recovery, and reliable improvement will be reported using (i) PHQ-9 only to align with depression research literature and (ii) both PHQ-9 and GAD-7, to align with IAPT practice. We will also report deterioration and reliable deterioration with regard to PHQ-9 and GAD-7 separately. We will also track symptoms weekly using the PHQ-9, GAD-7, Phobia Scale and the Work and Social Adjustment Scale.

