## Statistical methods

### Statistical methods for primary and secondary outcomes {20a}

All analyses will be carried out using an a priori statistical analysis plan as agreed with the TMG and TSC.

Participant characteristics at baseline (including number of previous depressive episodes and IAPT service) will be set out descriptively by the treatment arm. The primary analysis approach will use the intention-to-treat (ITT) principle (all participants will be included in the analysis according to their randomised allocation irrespective of the treatment actually received) including observed data only. All outcomes will be reported descriptively at baseline, and at 10 and 34 weeks’ follow-up. Continuous outcomes will be analysed using linear regression models. The binary outcome variables will be analysed using logistic regression. All analyses will adjust for participant covariates used in randomisation, with adjustment for baseline scores for continuous outcomes. We will assess other participant characteristics at baseline and will consider adjusting for any covariates that are found to be substantively unbalanced, should such covariates be considered predictive of outcome. Inferential between-group comparisons (MBCT vs TAU) for the primary and all secondary outcomes will be performed at 34-week follow-up. As a sensitivity analysis, we will perform a complier average causal effect (CACE) analysis for continuous outcomes only, to estimate the treatment effect while accounting for non-adherence to treatment. A participant in the intervention arm will be considered to be a ‘complier’, if a minimum of four treatment sessions were attended. Mixed effects regression models with a random effect on individual participant will be performed for continuous and binary outcomes, including participants with outcome data reported for at least one follow-up time. To address the potential for clustering effects by IAPT service, we will perform sensitivity analyses using mixed effects regression models for the primary and secondary (continuous and binary) outcomes, with a random effect on IAPT service. Similarly, to address the potential for effects of clustering by therapist, further sensitivity analyses will test for the effect of individual therapists or therapist seniority. Mixed effects model with a random effect on individual therapist will also be performed. As a further sensitivity analysis, therapist seniority will be added as a fixed effect within the primary model for the primary outcome and all secondary outcomes. To explore effects under conditions of different inclusion criteria, a sensitivity analysis will be run including only those patients who failed to meet both criteria for reliable recovery according to IAPT conventions, that is reliable change in symptoms and symptom levels below caseness. We will also perform a sensitivity analysis (primary outcome only) to include any data collected outside the 7-day window. Sensitivity analyses will be based on the ITT principle (except the CACE analysis). Should further sensitivity analyses be indicated, these will be described in the statistical analysis plan.

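### Hypothesis 1 expects a PHQ-9 difference at both 10 and 34 weeks, but the analysis section specifies no 10-week between-group comparison

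*Protocol article*

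**What the plan says.** Three places commit the trial to a 10-week comparison of the arms.

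- Protocol article, Hypotheses: "participants who receive MBCT will show significantly stronger reductions in depressive symptomatology than participants who receive TAU", and this is expected "both at 10 weeks post-randomisation (post-treatment; secondary outcome) and at 34 weeks post-randomisation (primary outcome".
- Background and rationale {6a}: "We shall test the immediate effects of the intervention on depressive symptomatology". The same sentence adds the question of whether effects last to the primary time point.
- Secondary outcomes: "Secondary outcomes include PHQ-9 measured at 10 weeks post-randomisation, and other clinical outcomes measured at 10-week and 34-week follow-up".

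The analysis section, Statistical methods for primary and secondary outcomes {20a}, fixes the time point of inference differently: "Inferential between-group comparisons (MBCT vs TAU) for the primary and all secondary outcomes will be performed at 34-week follow-up". On 10 weeks it says expressly only this: "All outcomes will be reported descriptively at baseline, and at 10 and 34 weeks’ follow-up". It also plans a repeated-measures analysis, open to anyone with an outcome at one or more follow-ups: "Mixed effects regression models with a random effect on individual participant will be performed for continuous and binary outcomes". No arm-by-time term and no contrast at a given visit is stated for that model.

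**The concern.** A hypothesis that uses the word significantly about a difference between arms needs a between-arm test at the time point it names. For 34 weeks there is one. For 10 weeks the analysis section names none, and the sentence that sets the time point of inference points elsewhere.

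The 10-week comparison bears on interpretation. The rationale section presents the design as asking whether there is an immediate effect and whether it lasts. If the 34-week difference is null, the benefit may have been gained and then lost, or there may never have been one. The two have different implications for adoption in IAPT, and only a comparison at 10 weeks separates them. If that comparison is first defined after results are known, the current wording of {20a} would count against calling it pre-specified.

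**Working it through.** **Step 1. Set the sections side by side.**

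| Section | 10-week PHQ-9 | 34-week PHQ-9 |
|---|---|---|
| Hypotheses | significant between-arm difference expected | significant between-arm difference expected |
| Background and rationale {6a} | immediate effect to be tested | sustained effect, primary |
| Secondary outcomes / Primary outcome | named secondary outcome | primary outcome |
| {20a}, descriptive reporting | yes | yes |
| {20a}, inferential comparison | none named | yes |

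The {20a} sentence cannot be applied literally to one of the outcomes it covers. The 10-week PHQ-9 is a secondary outcome, so it falls under the rule for all secondary outcomes, yet a 10-week score cannot be compared at 34 weeks. This is a conflict between statements, not merely an omitted detail.

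**Step 2. Ask whether the mixed model fills the gap.** Let d10 and d34 be the arm differences at the two follow-ups. With a participant random intercept, complete data at both visits and no arm-by-time term, the arm coefficient estimates (d10 + d34)/2. As an illustration with assumed effects:

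- d10 = 2.59, d34 = 0: (2.59 + 0)/2 = 1.295
- d10 = d34 = 1.295: (1.295 + 1.295)/2 = 1.295

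The model returns the same value for an effect gained and lost as for a smaller constant effect. It gives a 10-week estimate only if an arm-by-time term is added.

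**Step 3. Ask whether sample size is an obstacle.** Inputs from Sample size {14}: difference 2.59, SD 5.4, power 90%, alpha 0.05, 186 evaluable, 20% attrition, 234 recruited. Allocation is 1:1 ({16a}). Sidedness is not stated; two-sided reproduces the figure.

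- Normal approximation: n per arm = 2 × (1.960 + 1.282)² × (5.4/2.59)² ≈ 91.4, so 92 per arm, 184 in total.
- t-test version: 92.3, so 93 per arm, 186 in total. This matches the protocol.
- One-sided alpha gives 150 in total and does not match.
- Attrition: 93/0.8 = 116.25, so 117 per arm, 234 in total. This matches the protocol.

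If the same difference and SD held at 10 weeks, which is an assumption because the protocol gives no 10-week figures, a two-sided 0.05 test (normal approximation) would have power of about 90.5% with 93 per arm and about 95.6% with 117 per arm. This carries the 34-week design values over to another visit. It shows only that numbers are not the reason to omit the comparison.

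**The case against.** A reader might infer that the 10-week hypothesis will never be tested, or that the trial cannot answer it. The protocol does not support that, for four reasons.

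- The {20a} sentence places inference at 34 weeks but does not say that it happens only there.
- The same section states, without a time limit, that continuous outcomes are analysed by adjusted linear regression. The 10-week PHQ-9 is a continuous outcome and could fall under that rule.
- The descriptive sentence covers 34 weeks as well, where inference is certain, so it does not by itself make 10 weeks descriptive only.
- The mixed model admits participants with any follow-up and so implies that 10-week scores enter a regression. An a priori analysis plan is invoked and is not shown. It may define the contrast, and a contrast set there before results are seen would be pre-specified, since the outcome, time point, direction and comparator are already published.

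All of this stands, and it limits the point to saying that no 10-week contrast is specified. It does not remove the conflict. The general regression sentence gives the type of model, while the later sentence gives the time point, and the time point is 34 weeks. A plan that follows {20a} faithfully would inherit the mismatch with the hypothesis.

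It is also tempting to gate the 10-week test on a significant primary result. That would block a confirmatory reading in the very case where the comparison is most useful, a null result at 34 weeks. Adding p-values at 10 weeks for every other secondary outcome would go beyond hypothesis 1, which concerns depressive symptoms alone.

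**Conclusion.** The point holds in limited form. The hypotheses and rationale promise a between-arm test of PHQ-9 at 10 weeks, and the analysis section specifies none. One of the two time points in hypothesis 1 is affected. The primary outcome, its time point, alpha, sample size and primary analysis are not. This is a should-fix.

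The conclusion rests on the published text alone. The analysis plan, if it already contains a 10-week contrast, would resolve the matter in practice, though the protocol wording would still need to agree with it. The averaging result assumes complete data at both follow-ups and no arm-by-time term. The power figures assume that the 34-week design values apply at 10 weeks.

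**What to change.** Before any unblinded analysis, amend {20a} along these lines: the adjusted MBCT minus TAU difference in PHQ-9 at 10 weeks, with 95% CI, is a pre-specified secondary comparison. Estimate it either with the same linear regression as the primary (adjusted for baseline score and the minimisation factors) or as the 10-week contrast from the planned mixed model with an arm-by-time term. Name one of the two in advance. Report the result whatever happens at 34 weeks.

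Label it secondary, so that the primary alpha and the 234 recruited do not change. Two independent tests at 0.05 would carry a chance of at least one false positive of 1 − 0.95² = 9.75%. That matters only if either could be claimed as the trial's success, and the label rules this out.

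The other consistent repair is to reword the Hypotheses and the rationale so that 10-week results are descriptive. It removes the conflict but gives up a stated aim.

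The cost is an amendment of wording and one more secondary test. The 10-week questionnaires are already scheduled, so no new data are needed.

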
### Interim analyses {21b}

A Data Monitoring and Ethics Committee will look at outcome data regularly during data collection.

### Methods for additional analyses (e.g. subgroup analyses) {20b}

We do not a priori plan to conduct subgroup analyses.

### Methods in analysis to handle protocol non-adherence and any statistical methods to handle missing data {20c}

To investigate the effects of missing data, a further sensitivity analysis will use multiple imputation to impute missing outcome data for continuous outcomes only.

### Plans to give access to the full protocol, participant-level data and statistical code {31c}

Data sharing will be enabled using a controlled access model in line with Good Practice Principles for Sharing Individual Participant Data from Publicly Funded Clinical Trials from the UK Medical Research Council [42]. Scientists seeking to access the data for use in future projects must do so via request to the CI and projects using the data must have been approved in accordance with contemporary UK ethical and regulatory processes pertaining to the release of anonymised data under these circumstances. We will follow current recommendations on anonymising and curating trial data for sharing [43].

## Oversight and monitoring

### Composition of the coordinating centre and trial steering committee {5d}

The CI will assume responsibility for the overall management of the trial and delivery of the work. The CI will lead the core research team (including all site leads, the trial manager, and research assistants), who will meet monthly via videoconference and receive input from the wider research group and representatives of the Patient Advisory Group at quarterly Trial Management Group meetings. The Trial Management Group will monitor all aspects of the conduct and progress of the trial, ensure that the protocol is adhered to and take appropriate action to safeguard participants and the quality of the trial.

The trial is governed by a Trial Steering Committee (TSC), which is independent from the sponsor. The role of the TSC, which includes an independent chair and four other independent members, one of whom is an independent patient and public involvement representative, is to provide critical scrutiny to the conduct of the proposed research. [name] (University of Oxford) has kindly agreed to chair the TSC.

### Composition of the data monitoring committee, its role and reporting structure {21a}

We have set up an Independent Data Monitoring Committee (IDMC) comprising a chair ([name], University of York), an independent mental health statistician and a clinician. The IDMC will review serious adverse events that are thought to be trial- or treatment-related and look at outcome data regularly during data collection. As the TSC, the IDMC is independent from the sponsor and has no competing interests. The TSC and IDMC will meet on a half-yearly basis.

### Adverse event reporting and harms {22}

#### Risk monitoring

In order to identify risk issues, research assistants will screen questionnaires within 72 h of completion to check for increases in suicidality and any service use that may be indicative of a serious adverse event. A score of more than 0 on the PHQ-9 item 9 (that represents a change from the previous trial assessment) and reports of suicidal ideation, intent, plans or urges, and any risk of harm to self or others in the MINI interview or other contexts will be deemed as risk issues. Identification of a risk issue will trigger the trial team to capture more detailed information and context to assess risk in line with the trial risk protocol. Where necessary participants will be provided with support in line with the local sites’ risk management process.

In the MBCT arm, the site RA will routinely monitor PHQ-9 scores on a weekly basis prior to each session (or as soon after as possible in the event of participant non-completion) and immediately email the mindfulness teacher and PI if:A participant’s score has increased by 6 points or more from baseline assessment, specifying the amount of increase, and/orA participant scores 1 or more on item 9 of PHQ-9, specifying what the score is and whether this score is typical or represents a change

The mindfulness teacher or appropriate clinical delegate will follow the study risk protocol to ensure appropriate contact is made with the participant to discuss their mental state, current risk and what is needed to keep themselves safe. Information from this conversation will be considered by the therapist and PI to answer the question of whether a participant should continue with treatment. All instances in which the risk protocol has been enacted will be documented using the Risk Assessment Form and logged in the study risk management log together with contextual information and their classification.

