##### Unexpected adverse reaction (UAR)

An adverse reaction, the nature or severity of which is not consistent with the information about the trial intervention.

Serious adverse event (SAE) or serious adverse reaction (SAR) or suspected unexpected serious adverse reaction (SUSAR): Respectively any adverse event, adverse reaction or unexpected adverse reaction that:Results in deathIs life-threatening (where the term life-threatening refers to an event in which the patient is at risk of death at the time of the event; it does not refer to an event that might hypothetically cause death if it was more severe (e.g. a silent myocardial infarction))Requires inpatient hospitalisation or prolongation of existing hospitalisationResults in persistent or significant disability or incapacityConsists of a congenital anomaly or birth defectOr any other health event which in the opinion of the clinician is serious

Important adverse events that are not immediately life-threatening or do not result in death or hospitalisation but may jeopardise the subject or may require intervention to prevent one of the other outcomes listed in the definition above should also be considered serious.

As suicidal ideation and mild self-harm are a common aspect of the clinical presentation of many mood disorders, we will only rate these as adverse events if they include suicidal behaviour or the degree of self-harm puts the individual at risk of physical injury. In particular, suicidality will be deemed as an AE or SAE, if risk is categorised as level C on our risk protocol. Routine hospitalisations and planned surgery recorded at the baseline assessment visit (pre-treatment) do not require reporting as SAEs.

Any event observed by either a researcher or therapist that could be considered as SAE will be documented on the Serious Adverse Event Form and reported to the local PI. Research Assistants will be responsible for screening the AD-SUS questionnaire within 72 h of completion to check for potential serious adverse events. Identification of a potential SAE in the AD-SUS will trigger a telephone call to the participant to capture more detailed information and context of the event although this should not delay reporting. As reports on the AD-SUS are retrospective, the research team will assess any remaining risks and the local sites risk management process will be adhered to at any time to ensure participants receive support where necessary.

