The local PI will evaluate the reported event for seriousness considering the available contextual information. All non-serious AE will be documented in the electronic patient record. If the issue is assessed as serious, the event must be reported to the CI, Trial Manager, local R&D department and Sponsor, immediately and no later than 24 h of being made aware of the event. Initial reports of SAE can be made via email but must be promptly followed with a detailed written report using the Serious Adverse Event Reporting Form for the Sponsor and containing sufficient detail regarding concurrent life events. The PI should ensure that follow-up information is provided when available.

The sponsor will allocate an SAE number and forward the event to the trial’s Independent Clinician who is part of the Independent Data Monitoring Committee. The Independent Clinician will rate the event to confirm or question its seriousness, with the final decision in case of discrepancy made by the PI; determine the causality of SAEs according to Table 1; and also rate SAEs with regard to its expectedness. Independent review will be conducted within 72 h and the outcome will be reported back to the local Research Assistant PI, CI, Trial Manager and sponsor by email using the SAE number allocated by the sponsor.

**Table 1 Tab1:** SAE causality rating

Relationship	Description	Event type
Unrelated	There is no evidence of any causal relationship	Unrelated SAE
Unlikely to be related	There is little evidence to suggest that there is a causal relationship (e.g. the event did not occur within a reasonable time after administration of the trial treatment). There is another reasonable explanation for the event (e.g. the participant’s clinical condition or other concomitant treatment)	Unrelated SAE
Possibly related	There is some evidence to suggest a causal relationship (e.g. because the event occurs within a reasonable time after administration of the trial treatment). However, the influence of other factors may have contributed to the event (e.g. the participant’s clinical condition or other concomitant treatment)	SAR
Probably related	There is evidence to suggest a causal relationship and the influence of other factors is unlikely	SAR
Definitely related	There is clear evidence to suggest a causal relationship and other possible contributing factors can be ruled out	SAR

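### Weekly suicidality checks with wider triggers are written for the MBCT arm only, so a by-arm count of level C suicidality is open to detection bias against MBCT, of unknown size (minor)

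*Protocol article*

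**What the plan says.** All references are to the protocol article.

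**Both arms.** Under Risk monitoring, questionnaires are screened within 72 hours. The item-9 rule is "A score of more than 0 on the PHQ-9 item 9 (that represents a change from the previous trial assessment"), so a stable positive score does not qualify. Risk disclosed at the MINI interview or on other occasions also counts. The AD-SUS is screened too: "Identification of a potential SAE in the AD-SUS will trigger a telephone call to the participant".

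**MBCT arm only.** The same section continues: "In the MBCT arm, the site RA will routinely monitor PHQ-9 scores on a weekly basis prior to each session". The teacher and PI are alerted if the total has risen 6 or more points from baseline, or if a "participant scores 1 or more on item 9 of PHQ-9, specifying what the score is and whether this score is typical" or changed. The teacher or a clinical delegate then contacts the participant under the risk protocol.

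**Link to adverse events.** The adverse event definitions state: "In particular, suicidality will be deemed as an AE or SAE, if risk is categorised as level C on our risk protocol".

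**Observers and records.** "Any event observed by either a researcher or therapist that could be considered as SAE will be documented on the Serious Adverse Event Form". Under Intervention description {11a}, trial therapists deliver MBCT. On records, "All instances in which the risk protocol has been enacted will be documented using the Risk Assessment Form" and logged with context and classification, while "All non-serious AE will be documented in the electronic patient record".

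**TAU contact.** Intervention description {11a}, Strategies to improve adherence {11c} and Participant timeline {13} give both groups an interview after allocation. Plans for assessment {18a} makes the post-treatment and follow-up assessments questionnaire-only. Secondary outcomes says symptoms are tracked weekly, including by PHQ-9, and names no arm.

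**The concern.** The level C rating that defines a suicidality AE or SAE is reached through the risk protocol, and the written ways into that protocol differ by arm in three respects: how often item 9 is looked at, what sets off an alert, and who is watching. If true risk is equal, the arm that is looked at more often will tend to record more events.

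Suicidality is a central harm in currently depressed patients, and the trial is meant to inform IAPT practice. A harms table showing an MBCT excess that arises from closer observation could count wrongly against the treatment. Because this is a data-collection rule, an analysis plan can separate the routes later only if the route was recorded at the time.

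**Working it through.** The plan gives no figure for adverse event rates or detection, so there is nothing of its own to reproduce. The check compares the routes and then illustrates the possible size.

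**Step 1. Routes as written, after randomisation**

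| Route | MBCT | TAU |
|---|---|---|
| Pre-intervention interview | yes | yes |
| 10- and 34-week questionnaires, item 9 positive and changed | yes | yes |
| AD-SUS screen | yes | yes |
| Disclosure on other occasions | yes | yes |
| Weekly PHQ-9 check, any item-9 score of 1 or more, or 6-point rise | yes, around 8 sessions | not written |
| Trial therapist as observer | yes | none (inferred: trial therapists treat only MBCT) |

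Scheduled item-9 checks as written: 8 + 2 = 10 in MBCT against 2 in TAU, plus one interview in each arm.

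**Step 2. Which differences matter.** A trigger is not an adverse event, and the wider item-9 rule mainly adds stable scores, so that part is probably small. The therapist part is not quantified. Frequency can be illustrated.

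**Step 3. Illustration.** Assumptions, none from the protocol unless marked:
- true risk is equal in both arms; onset is uniform over 34 weeks (follow-up length from the protocol); duration is exponential with mean D = 2, 4 or 8 weeks;
- looks at weeks 10 and 34 in both arms (protocol), plus weeks 2 to 9 in MBCT (assumed session weeks);
- TAU is not screened weekly;
- every look is completed and fully sensitive, with look-back L = 0 or 2 weeks;
- the interview reveals nothing, or acts as a look in both arms at week 1 or week 2.

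For a gap g between looks, the expected detected onset time is min(L, g) + D[1 − exp(−max(g − L, 0)/D)]. Summing over gaps and dividing by 34 gives the detection probability.

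Worked case, D = 2, L = 0, uninformative interview:
- TAU, gaps 10 and 24: (1.987 + 2.000)/34 = 0.117.
- MBCT, gaps 2, eight of 1, and 24: (1.264 + 8 × 0.787 + 2.000)/34 = 0.281.
- Ratio 2.40.

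With an informative interview at week 1:
- TAU, gaps 1, 9 and 24: (0.787 + 1.978 + 2.000)/34 = 0.140.
- MBCT, ten gaps of 1, and 24: (7.869 + 2.000)/34 = 0.290.
- Ratio 2.07. At week 2 it is 0.281/0.154 = 1.83.

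Ratios of recorded events, MBCT to TAU, with no other common capture:

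| Look-back | Interview | D = 2 | D = 4 | D = 8 |
|---|---|---|---|---|
| 0 | uninformative | 2.40 | 1.65 | 1.27 |
| 0 | week 1 | 2.07 | 1.52 | 1.22 |
| 0 | week 2 | 1.83 | 1.40 | 1.17 |
| 2 weeks | uninformative | 1.76 | 1.40 | 1.18 |
| 2 weeks | week 1 | 1.57 | 1.30 | 1.14 |
| 2 weeks | week 2 | 1.41 | 1.22 | 1.10 |

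**Step 4. Capture by routes common to both arms.** If a share c of episodes is caught anyway in both arms (AD-SUS, other disclosure), detection becomes 1 − (1 − p)(1 − c). With c = 0.5, D = 2, L = 0 and an uninformative interview: MBCT 0.641, TAU 0.559, ratio 1.15. Across all rows above, c = 0.5 gives 1.03 to 1.15 and c = 0.75 gives 1.01 to 1.05.

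**Step 5. If TAU is screened weekly too,** the looks are the same and the frequency ratio is 1.0.

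In counts, with an assumed 10% risk in 117 per arm (11.7 episodes), week-1 interview, D = 2, L = 0 and c = 0: 11.7 × 0.290 = 3.4 against 11.7 × 0.140 = 1.6. The ratios do not depend on the 10%.

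**The case against.** **TAU may be screened weekly.** The weekly tracking under Secondary outcomes and the 72-hour screen carry no arm restriction, and the schedule figure that might settle the matter is not available here. This stands: the frequency component may not exist. The any-score and 6-point alerts and the teacher contact would still be written for MBCT only.

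**TAU is not unobserved after baseline.** A reader might infer from the questionnaire-only follow-up that no interview takes place after baseline. The documents do not support that, since both groups have a pre-intervention interview. The text does not say that risk is asked about there, so it is a possible route.

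**The model is crude.** Level C concerns behaviour or self-harm risking injury, not lasting ideation, and acts leading to service use can surface through the AD-SUS in both arms. This stands and favours the lower ratios. Any bias should fall mainly on events without service use.

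**The direction is not certain.** Weekly contact may prevent escalation to level C, which would lower the MBCT count. This stands.

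**The forms are not shown and no by-arm harms comparison is stated.** Both are true. The forms may already capture the route, and the point applies only if events are counted by arm.

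**Trial decisions.** A reader might infer that the halt rule or the IDMC's case review is biased. The text does not support this: both turn on whether an individual event is judged related, so the effect is at most indirect, through more MBCT cases reaching review.

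**Conclusion.** The point holds as a minor harms-reporting issue. Following the text exactly, MBCT participants have more routes into the rating that defines a suicidality AE or SAE, and a by-arm count is open to detection bias against MBCT.

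The size cannot be fixed from the protocol. It runs from no frequency bias (TAU screened weekly), through about 1.0 to 1.15 (half or more of episodes caught by common routes), to about 1.8 to 2.1 (2-week episodes, current state only, no such capture, one informative interview), or 2.4 if the interview reveals nothing. These figures rest on assumed episode lengths, look-back and complete, fully sensitive checks. The trigger and therapist differences, and any preventive effect of weekly contact, are not quantified. A firm claim that MBCT events will be doubled is not supported. The primary outcome is unaffected.

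**What to change.** 1. Under Secondary outcomes, state which arm completes the weekly measures. If both do, apply the same item-9 trigger to both.
2. If the forms do not already do so, record how each event was detected (interview, scheduled questionnaire, AD-SUS, weekly check, therapist, other) on the Risk Assessment Form, the Serious Adverse Event Form and the record of any non-serious suicidality AE.
3. In any by-arm harms report, show all events. Beside them show those found by, or also evident through, the common routes: the pre-intervention interview, the 10- and 34-week questionnaires (item-9 change measured from the previous scheduled assessment), and the AD-SUS. List detections made only by the weekly check or only by a therapist separately.
4. Keep the weekly MBCT checks for clinical safety.

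The cost is one field on existing forms and two or three sentences, with no extra participant assessments. The common-route count is smaller and less precise, so both counts must be shown. It also cannot correct for episodes that weekly contact resolved before week 10.
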